### Interventions

2.2

During treatment, according to the Dutch guideline for low back pain, patients in the intervention and control group are asked to walk and/or cycle outdoors in accordance with the DSHPA (Hildebrandt et al., 2007).

In the intervention group illness beliefs according to Leventhal's Common‐Sense Model of self‐regulation will be discussed with the patient and the partner or friend (Siemonsma et al., 2013). During two half‐hour consultations maladaptive beliefs and feelings about low back pain are mapped in a standardized dialogue, maladaptive beliefs are challenged, evidence‐based beliefs as an alternative are formulated, and the utility is tested to become physically active according the DSHPA (Siemonsma et al., 2013). Organization of social support by a partner or friend is added. In a standardized discussion the partner or friend of the patient will be advised to organize social support for executing the activity advice.

In the control group only the illness beliefs according to Leventhal's Common‐Sense Model of self‐regulation will be discussed with the patient and the partner or friend (Siemonsma et al., 2013).

Only when requested by the patient the intervention will be discontinued.

### Outcomes

2.3

#### Baseline information

2.3.1

At baseline age, gender and education level will be registered.

To assess whether comorbidity influence adherence to an activity advice the medical burden of chronic illness is assessed with the Cumulative Illness Rating Scale (CIRS) (Appendix 1). The CIRS ranges from 0 (no illness) to 52 points and is a valid and reliable scale to measure comorbidities in clinical research (de Groot, Beckerman, Lankhorst & Bouter, 2003; Fortin et al., 2005).

It is hypothesised that overweighted/obese patients are protentional physical inactive. BMI of the patient will be calculated and categorized according to the WHO criteria (WHO, 2000).

It is hypothesised that the number of recurrences of low back pain influence adherence to an activity advice negatively, therefore, the number of recurrences of periods of low back pain will be noted.

To assess whether perceived pain and/or disability influences adherence to the activity advice, the visual analogue scale (VAS) for pain and the Quebec Back Pain Disability Scale (QBPDS) for disability will be used at baseline, both of which have been validated for assessing pain and disability (Bijur et al., 2001; Boer et al., 2004; Chapman et al., 2011; Smeets, Köke Lin, Ferreira & Demoulin, 2011) (Appendix 1).

Patients who refuse to enter the study will be asked to fill in the questionnaire at baseline (Appendix 1). The refusal questionnaire (RQ) is a study specified questionnaire collecting 13 reasons of refusal for entering the study (Barnes et al., 2012; Barratt et al., 2013; Williams et al., 2007).

#### Primary outcome

2.3.2

Adherence to the activity advice according to the DSHPA is the primary outcome measure and will be measured by a 3D accelerometer (Activ8, 2M engineering, Valkenswaard, the Netherlands). During the assessment periods at one, six‐ and 12‐week patients are instructed to wear the Activ8 every day during one week. The number of days per week patients have walked or cycled according to the advice will be counted. Cut‐off for adherence will be set at a minimum of 5 times per week of at least 30 min walking and/or cycling. The Activ8 system is a valid instrument to quantify body postures and motions (Fanchamps et al., 2018). For this study only the walking and cycling activities recorded by the monitor will be used for analyses.

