**Methods:**

In a randomized controlled clinical trial, in private physiotherapy practices in the Netherlands, patients ≥18 years presenting with at least a second episode of nonspecific low back pain will be randomized over two groups: activity advice and social support as an add‐on to usual care versus usual care alone. The primary outcome measure is adherence to an activity advice measured by an activity monitor at 1, 6 and 12 weeks. All other objectives will be measured by questionnaires.

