## INTRODUCTION

1

It seems that nonspecific low back pain (NSLBP), particularly with a recurrent or persistent course, cannot be successfully treated with a single intervention of any kind (Friedly et al., 2010). A positive effect of an active lifestyle including physical activities is reported on pain and disability (Choi et al., 2010; Dahm et al., 2010; Hendrick et al., 2011; Ooijendijk, Wendel‐Vos & de Vries, 2007; Smith & Grimmer‐Somers, 2010; Staal et al., 2013; van Middelkoop et al., 2010; van Middelkoop et al., 2011; Wai et al., 2008). Therefore, advising an active lifestyle to patients seems logical, and optimal patient adherence to this advice is necessary to be successful in managing NSLBP. As clinical practitioners we experience patients' poor adherence to physical activity recommendations every day. This experience is supported by conclusions in literature that many sufferers do not seem to adhere to their physiotherapist's advice (Beinart et al., 2013; Kolt & McEvoy, 2003).

Poor treatment adherence in patients managed in physiotherapy outpatient settings is associated with low levels of physical activity, low self‐efficacy, perceived illness beliefs, depression, anxiety, helplessness, poor social support, long treatment duration, and increased pain levels during exercise (Jack et al., 2010; Medina‐Mirapeix, Escolar‐Reina, Gascón‐Cánovas, Montilla‐Herrador, & Collins, 2009; Medina‐Mirapeix, Escolar‐Reina, Gascón‐Cánovas, Montilla‐Herrador, Jimeno‐Serrano, & Collins, 2009). Besides, there is limited or conflicting evidence on the influence of clinical signs to adherence such as pain and disability, comorbidity, obesity, and number of episodes of health threat (Jack et al. 2010). To increase patient relevant outcomes as pain and disability, it is necessary to invent new, simple applicable treatment options to overcome the adherence issue. These options should influence reasons for suboptimal adherence.

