### Participants

2.1

The trial will be performed in 20 private practices for physiotherapy in the Netherlands. Dutch people have access to their physiotherapist without a referral of their GP. People with an additional insurance are compensated for the costs. For this study physical inactive patients with low back pain are needed. It is hypothesized that patients having more than one episode of NSLBP are potentially more inactive compared to patients with a first episode, therefore patients with a first episode of low back pain will be excluded. Patients ≥18 years presenting with a self‐reported second episode (or more) of NSLBP are recruited for the study. Eligible patients will be recruited for the study together with their partner or friend. Patients will be excluded for the study if (1) they cannot bring a partner or friend, (2) they are unable to read, write or speak the Dutch Language, (3) they present red flags as mentioned in the Dutch low back pain guideline (Staal et al., 2013) or, (4) when presenting with a medical history of cancer, osteoporosis, rheumatoid arthritis, tuberculosis, trauma and fractures in the lumbar spine as well as recent musculoskeletal system infections (Henschke et al., 2009; Staal et al., 2013). Only physically inactive NSLBP sufferers will be included, therefore, patients adhering to the Dutch Standard Healthy Physical Activity (DSHPA) which prescribes being moderately active for at least 150 min per week will be excluded as well (Hildebrandt, Bernaards & Stubbe, 2007).

Eligibility criteria for participating physiotherapists are: (1) being a certified graduate physiotherapist, (2) being instructed and updated on the content of the study.

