### Timeline

2.4

Eligible patients will be recruited for the study together with their partner or friend by the assessing physiotherapist and will receive information about the study. If patients and partners or friends decide after 1 week of consideration they want to be included in the study, written informed consent will be asked to the patient and partner or friend and base‐line assessment of the patient and partner or friend will be performed (Appendix 1). After base‐line assessment the assessor explains to the patient that further treatment will be performed by an IGP or CGP. The patient will be contacted within 2 days for an appointment with either the IGP or CGP. The patient and partner/friend will be instructed to come both to the next two appointments. The assessor contacts the randomization centre. The randomisation centre allocates the patient for IGP or CGP and informs the assessor. The assessor instructs the IGP or CGP to make the next appointments with the patient and their partner/friend.

After the first intervention on illness beliefs with or without organizing social support, treatment will be applied according to the Dutch guideline for low back pain (Staal et al., 2013). In both groups' patients are instructed in executing the activity advice in accordance with the DSHPA and to wear a move monitor for 1 week (Hildebrandt et al., 2007). In the group in which the social support is given, the partner/friend will be asked to make a week schedule of times, activities, and contact‐control moments for the coming months.

At the end of the week the activity monitors will be returned, and questionnaires will be filled out. The second intervention on illness beliefs with or without organizing social support takes place and treatment will be applied according to the Dutch guideline for low back pain (Staal et al., 2013). After six‐ and 12‐weeks patients will be invited by the assessors to wear the Active8 for one week and to fill in the questionnaires. During the study period the IGP contacts the partner/friend in week 6 and 10 to evaluate whether social support was given. At the last appointment also the partner or friend will be invited and asked to fill in questionnaires. Enrolment of the study is shown in the flow diagram (Figure 1).

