### Statistical methods

2.9

To analyse the data SPSS version 25.0 (IBM SPSS, Chicago, IL, USA) will be used. For demographic data descriptive statistics will be used and normality assumptions for the variables will be checked. An intention‐to‐treat analysis will be used for the main outcome. To correspond to the primary aim of the study, outcomes of the Activ8 will be dichotomized into adherent and not adherent patients in the intervention and control group. The Chi^2^ test will be used to investigate if there is a significant difference in the proportion of adherent patients to the activity advice between the intervention and control group after one, six and 12 weeks, and if there is a significant difference in the proportion of adherent patients between patients who experienced social support or not on the social support scale after 12 weeks. A Time Series Analysis will be used to present changes over time in perceived illness beliefs of patients and partner/friend. To understand whether illness beliefs influence adherence, Pearson's r between outcomes of the IPQ‐S at baseline and after 12 weeks and (non)adherence measured by the Active8, will be calculated, and linear regression will be used for modelling the relationship between these outcomes. To assess the correlation between attitude and intention to physical activity (MAI) and adherence at 12 weeks, Pearson's will be calculated, and linear regression will be used for modelling the relationship between these outcomes. Influence of age, gender, education level, comorbidity (CIRS), pain (VAS) and disability (QBPDS) on adherence, will be estimated by multiple regression analyses. A *p* value of <0.05 will be considered statistically significant.

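### The primary test is fixed as an unadjusted chi-square that leaves out the randomisation strata, and no pre-treatment activity value is listed: valid, but some precision and a balance check are lost

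*Protocol article*

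**What the plan says.** The abstract defines the primary outcome as "adherence to an activity advice measured by an activity monitor at 1, 6 and 12 weeks". Section 2.3.2 (Primary outcome) adds that at each assessment "patients are instructed to wear the Activ8 every day during one week", and that a patient counts as adherent with a "minimum of 5 times per week of at least 30 min walking and/or cycling".

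Section 2.4 (Timeline) places the first monitor week after allocation and the first treatment session. At that point "patients are instructed in executing the activity advice in accordance with the DSHPA and to wear a move monitor for 1 week".

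Section 2.3.1 (Baseline information) opens with "At baseline age, gender and education level will be registered" and adds comorbidity (CIRS), BMI, number of recurrences, pain (VAS) and disability (QBPDS). Section 2.3.3 adds illness perceptions (DIPQ-S) and attitude and intention (MAI) at baseline. None of these measures activity.

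Section 2.1 (Participants) excludes patients who already meet the Dutch activity standard, "which prescribes being moderately active for at least 150 min per week will be excluded as well". The Introduction states: "Poor treatment adherence in patients managed in physiotherapy outpatient settings is associated with low levels of physical activity".

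Section 2.7 stratifies randomisation by BMI and number of previous episodes. Section 2.9 (Statistical methods) says that the chi-square "test will be used to investigate if there is a significant difference in the proportion of adherent patients to the activity advice" between the two groups. The strata do not enter this test. The separate regression on influences lists age, gender, education, CIRS, VAS and QBPDS, and does not list prior activity.

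**The concern.** The outcome is an activity status reached at follow-up. Before treatment, patients may range from sedentary to just under the entry limit, and the listed data do not distinguish them. If prior activity predicts later adherence, as the Introduction suggests, a chance difference between the arms adds noise to the primary result. Nobody could see that difference in a baseline table or allow for it.

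The strata raise the same issue in a simpler form. Section 2.7 chose BMI and episode count because such patients may be less active and less receptive. The design balances the two factors and the stated test then discards them, although both values exist for every randomised patient.

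At stake are precision, a balance check, and the secondary question of what influences adherence.

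**Working it through.** **1. Is there any pre-treatment activity value?** Setting sections 2.3.1, 2.3.3 and 2.4 side by side: the listed baseline items are age, gender, education, CIRS, BMI, recurrences, VAS, QBPDS, DIPQ-S and MAI. MAI covers attitude and intention, not activity. The week-1 monitor reading comes after treatment has begun. So none is listed.

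**2. How do entry and outcome relate?** Entry requires less than 150 min per week of moderate activity. Adherence requires 5 × 30 = 150 min per week of walking or cycling. Most patients therefore start below the outcome cut-off, but at unknown distances from it.

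**3. Size of a chance imbalance.** Inputs: 142 evaluable patients (section 2.5), with 1:1 allocation assumed, so 71 per arm. The difference in baseline means has SD √(2/71) = 0.168 baseline SDs. Assume control adherence of 31% on a normal latent scale (density at that cut-off 0.353) and a baseline-outcome correlation r = 0.3. A one-SD imbalance then moves adherence by 0.168 × 0.3 × 0.353 = 0.018, or 1.8 percentage points. With 31% versus 54%, the standard error of the difference is √(0.31×0.69/71 + 0.54×0.46/71) = 0.081, or 8.1 points. The imbalance is part of that ordinary sampling error, not an addition to it.

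**4. Power with and without adjustment.** The plan gives no adherence rates and calls the effect medium without a number. Its 142 does not follow from conventional medium effects at 5% and 80% power (w = 0.3 with 1 df gives 88; h = 0.5 gives 126). That is a separate matter. For this check I assumed 30% versus 53%, a pair that does give 142:

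- [1.96·√(2×0.415×0.585) + 0.842·√(0.30×0.70 + 0.53×0.47)]² / 0.23² = (1.366 + 0.570)² / 0.0529 ≈ 70.9, so 71 per arm.

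Latent-normal simulation, 2,500 runs per setting, complete data:

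| Assumed r | Unadjusted chi-square | Logistic, adjusted for baseline activity |
|---|---|---|
| 0 | 80% | 81% |
| 0.3 | 79% | 82% |
| 0.5 | 80% | 88% |
| 0.7 | 81% | 93% |

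A second set at 31% versus 54% gave 80.6% vs 80.8% at r = 0.1, 82.3% vs 83.2% at r = 0.2 and 80.4% vs 82.8% at r = 0.3. The simulation error of each power figure is about √(0.8×0.2/2500) = 0.8 points.

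**5. Type I error.** With 30% in both arms, rejection was 4.6% to 5.7% unadjusted and 4.7% to 5.4% adjusted. Both are at the nominal level.

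**6. If half the values are missing** (an assumption; missing indicator used): 81.2% vs 81.9% at r = 0.3 and 81.1% vs 83.5% at r = 0.5.

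The gain from the two strata was not simulated, because the documents give no association between them and adherence.

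**The case against.** The planned randomised comparison is valid as it stands, and a covariate-adjusted model can be called a preference. The validity part stands in full.

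A reader might infer that the missing baseline biases the primary result. The documents do not support that: randomisation is concealed, and the simulated type I error is about 5%.

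A reader might also take prior activity to be the strongest predictor of adherence. The Introduction lists it among several correlates without ranking them. Entry only below 150 minutes narrows its range and self-report blurs it, so the lower correlations are the more plausible ones.

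Nor can it be assumed that weekly minutes are already known at screening. Section 2.1 needs only a judgement of whether the limit is met, and a yes/no question would do. Recording minutes may therefore mean a new question. The intake forms and Appendix 1 are not shown and may hold the answer, but the stated analysis would still not use it.

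The design partly covers the issue, since the strata were chosen as proxies for inactivity and MAI is collected at baseline. That, however, is a reason to use the strata in the analysis.

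Timing also counts. Recruitment is scheduled from October 2016 to December 2022 and the article cites a 2020 source, so many patients may have been enrolled without the value.

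Finally, model details are often left to an analysis plan that is not shown. Here, though, section 2.9 names the primary test, so the point concerns a stated choice.

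**Conclusion.** The point holds as one of efficiency and transparency. The stated primary test leaves out strata already available for every patient, and the listed baseline data lack a variable that the protocol itself links to adherence. The comparison between arms remains unbiased.

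The gain from adding baseline activity is about 0 to 3 points of power for r up to 0.3, and about 6 to 8 points at r = 0.5 with complete data. It falls to roughly 1 to 2.5 points for r of 0.3 to 0.5 if half the values are missing. With self-report and the cut-off at 150 minutes, the lower end is the likelier. These figures rest on assumed adherence rates, 1:1 allocation, a normal latent scale and an assumed correlation.

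Using the strata is justified whether or not the activity item is added.

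**What to change.** **Section 2.9.** Analyse 12-week adherence with a logistic model containing treatment, BMI stratum and episode stratum, and report a standardised risk difference with its confidence interval. This keeps the answer on the scale of the planned difference in proportions. Use the stratum values as applied at randomisation, because the BMI bands printed in section 2.7 (<25, >24) overlap. This part needs no new data.

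**Section 2.3.1.** When the 150-minute criterion is applied, record the patient's weekly minutes of activity. Show them by arm in the baseline table and add them to the model as a continuous covariate, with a missing indicator for patients already enrolled without them. No baseline Activ8 week is needed.

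**Cost.** One self-report item per patient and one covariate. The item may be new if screening is now yes/no, its range stops at 150 minutes, and its benefit shrinks with each patient already enrolled without it. In the simulation, adjusting for a useless covariate (r = 0) cost no power. The change should be fixed in an amendment or the analysis plan before outcomes are compared by arm.

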#### Secondary outcomes

2.3.3

The Social Support Scale is a study specific questionnaire and assesses the rate of social support perceived by the patient and performed by the partner (Appendix 1). This questionnaire must be filled in by the patient and the partner after the investigation period and has dichotomous outcomes.

The Dutch Illness Perceptions Questionnaire Short‐form (DIPQ‐S) assesses patients' and partner/friends' illness beliefs (Appendix 1). Eight items about illness beliefs are scored on a 0–10‐point scale, one item is an open question. The questionnaire has good reliability and validity (Broadbent et al., 2006; de Raaij, Schröder, Maissan, Pool & Wittink, 2012; Leysen et al., 2015). The DIPQ‐S will be filled in at baseline, 1, 6 and 12 weeks follow up by the patient and at baseline, 1 and 12 weeks follow up by the partner or friend.

The module attitude and intention (MAI) of The Knowledge, Attitude, Self‐efficacy and Self‐regulation, Exercise and Social Support for Sports and Exercise Questionnaire will be used to assess attitude and intention to be physically active (Wink, van Woerkom & Renes, 2006). Attitude (6 items) can be scored from 6 (most negative) to 42 points (most positive), while intention (3 items) can be scored from 3 (most negative) to 21 points (most positive). Validity of this questionnaire is unknown, but it was used in the FLASH! Campaign from the Dutch Institute for Sport and Exercise in 2003–2006 (Appendix 1). This questionnaire will be filled in at baseline and after 12 weeks by the patient and partner or friend.

### Timeline

2.4

Eligible patients will be recruited for the study together with their partner or friend by the assessing physiotherapist and will receive information about the study. If patients and partners or friends decide after 1 week of consideration they want to be included in the study, written informed consent will be asked to the patient and partner or friend and base‐line assessment of the patient and partner or friend will be performed (Appendix 1). After base‐line assessment the assessor explains to the patient that further treatment will be performed by an IGP or CGP. The patient will be contacted within 2 days for an appointment with either the IGP or CGP. The patient and partner/friend will be instructed to come both to the next two appointments. The assessor contacts the randomization centre. The randomisation centre allocates the patient for IGP or CGP and informs the assessor. The assessor instructs the IGP or CGP to make the next appointments with the patient and their partner/friend.

After the first intervention on illness beliefs with or without organizing social support, treatment will be applied according to the Dutch guideline for low back pain (Staal et al., 2013). In both groups' patients are instructed in executing the activity advice in accordance with the DSHPA and to wear a move monitor for 1 week (Hildebrandt et al., 2007). In the group in which the social support is given, the partner/friend will be asked to make a week schedule of times, activities, and contact‐control moments for the coming months.

At the end of the week the activity monitors will be returned, and questionnaires will be filled out. The second intervention on illness beliefs with or without organizing social support takes place and treatment will be applied according to the Dutch guideline for low back pain (Staal et al., 2013). After six‐ and 12‐weeks patients will be invited by the assessors to wear the Active8 for one week and to fill in the questionnaires. During the study period the IGP contacts the partner/friend in week 6 and 10 to evaluate whether social support was given. At the last appointment also the partner or friend will be invited and asked to fill in questionnaires. Enrolment of the study is shown in the flow diagram (Figure 1).

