During the first meeting all physiotherapists will be informed about the Dutch guideline for low back pain (Staal et al., 2013) and state of the art knowledge, to provide that treatment during the study will be in accordance with the guideline. Before the second meeting participating physiotherapists will be divided into three groups: in every clinic, an Assessor Physiotherapist (AP), an Intervention Group Physiotherapist (IGP) and a Control Group Physiotherapist (CGP) is needed. The second meeting will be for AP's, IGP's and CGP's separately. The AP's will be trained in knowledge about the study, inclusion criteria, exclusion criteria, informed consent, standardized intake forms and assessments. They will be trained how to communicate about the study in a positive manner to the patient and partner/friend. It will be explained to the physiotherapists how to adhere to the allocation procedure and how to register all investigational procedures and the use of the activity monitor. Participating CGP's will be instructed on the background and rationale of the study, treatment of illness beliefs, the activity advice, and the use of the activity monitor. Participating IGP's will be instructed on the same elements with an additional short course on how to motivate the patient and their partner/friend in organizing social support. Some participating physiotherapists are students Orthopaedic Manipulative Physical Therapy at the Rotterdam University of Applied Sciences, Rotterdam, The Netherlands. They participate in this study as APs where they must conduct a management assignment as part of their Master of Science educational program.

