## DISCUSSION

3

This project is the first comprehensive research project to assess whether social support influences adherence to an activity advice outside the clinical setting without supervision of a healthcare provider. Unique in this study is that intervening on illness beliefs will be provided to patient and partner to minimize the influence of maladaptive illness beliefs on adherence. Literature mentions that intervention on illness beliefs changes outcomes of the DIPQS, however, responsiveness of the questionnaire is lacking (Broadbent et al., 2015). Despite this, it is of interest if a tendence of change over time may occur and influence outcomes of adherence.

Where evidence on clinical barriers is conflicting and limited, complementary, influence of age, gender, education level, comorbidity, attitude and intention to physical activity and perceived pain and disability on adherence will be investigated. Findings have implications for the management of patients with low back pain, enabling prediction as to which low back pain patient giving an activity advice with social support makes sense.

It is important to note the variation in how concepts of (non)adherence are operationalized in existing literature resulting in variable outcomes (Essery et al., 2017; van Koppen et al., 2020). For robust outcomes in this study an accurate definition of the activity advice is applied, mentioning frequency and duration, and outcomes of adherence are dichotomous, measured with a validated move monitor.

Strengths of the study are the concealed allocation and the randomization. To reduce the presence of observer bias, measurements will not be performed by the treating physiotherapist.

Treatment of both groups in one physiotherapy practice is preferred to overcome selection bias. This implicates that despite the standardized protocol and the strict requirements to ensure blinding, it is possible that patients and treating physiotherapist exchange information about the interventions. This may influence outcomes and is therefore a limitation of the study.

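### Week 1 measures adherence after only one of the two planned sessions, yet has the same primary standing as weeks 6 and 12

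*Protocol article*

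**What the plan says.** Section 2.2 plans two half-hour consultations on illness beliefs. The intervention arm adds the organisation of social support by a partner or friend.

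Section 2.4 (Timeline) gives the order of events:

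- The first session opens the sequence: "After the first intervention on illness beliefs with or without organizing social support, treatment will be applied according to the Dutch guideline".
- In both groups "patients are instructed in executing the activity advice in accordance with the DSHPA and to wear a move monitor for 1 week". In the intervention arm the partner or friend is also asked to draw up a schedule covering the following months.
- Then "At the end of the week the activity monitors will be returned, and questionnaires will be filled out".
- Then "The second intervention on illness beliefs with or without organizing social support takes place".
- At six and 12 weeks "patients will be invited by the assessors to wear the Active8 for one week and to fill in the questionnaires".

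The Abstract and section 2.3.2 (Primary outcome) list 1, 6 and 12 weeks for the primary measure without ranking them. Section 2.9 (Statistical methods) applies the chi-square test to the proportion adherent "between the intervention and control group after one, six and 12 weeks", with significance at p < 0.05. Section 2.5 (Sample size) refers only to the effect after 12 weeks.

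**The concern.** The primary objective asks whether patients randomised to social support adhere better to the activity advice. The intervention that is meant to achieve this is delivered in two sessions, and section 2.4 attaches the social support element to both. The week-1 window closes before the second session, so it cannot show what the full planned delivery achieves.

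Given equal standing, week 1 can mislead in two ways. A significant difference at week 1, not sustained at week 12, could be reported as success on the primary objective although only half of the sessions had been given. A null week-1 result could be counted against social support on the same footing as a null at week 12. The article has no rule that prevents either reading.

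**Working it through.** This point rests on order and status, so the check sets the sections side by side.

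**1. Sessions completed before each window** (sections 2.2 and 2.4; two sessions planned)

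| Window | Sessions before it | Share |
|---|---|---|
| Week 1 | 1 of 2 | 1/2 = 50% |
| Week 6 | 2 of 2 | 2/2 = 100% |
| Week 12 | 2 of 2 | 2/2 = 100% |

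These shares count sessions. They do not measure how much social support was delivered.

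**2. Is the randomised element split across both sessions?** Section 2.2 uses the two consultations to describe the illness-beliefs treatment, which both arms receive. Section 2.4, however, says of the first and again of the second session that it comes with or without organising social support. The randomised element is therefore also given in two parts, and the second part comes after the week-1 window.

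**3. Standing of each window**

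| Place | Week 1 | Week 6 | Week 12 |
|---|---|---|---|
| Abstract, primary outcome | listed | listed | listed |
| 2.3.2 Primary outcome | listed | listed | listed |
| 2.9 chi-square test | tested | tested | tested |
| 2.5 Sample size | no | no | yes |

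Only the sample size separates the three time points, and it points to week 12.

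**4. What the analysis allows.** Under section 2.9 each of the three tests can be significant at p < 0.05, and none is named as decisive. A week-1 difference alone would therefore meet the stated criterion on the primary outcome.

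**5. Figures.** The plan attaches no figure to week 1. Its sample size (142, or 163 with drop-out) is tied to 12 weeks and does not change with the status of week 1. The 142 does not reproduce from a conventional medium effect at two-sided alpha 0.05 and 80% power: 7.849 / 0.3² = 87.2, so 88 in total, for w = 0.3 with 1 df; and 2 × ((1.960 + 0.842) / 0.5)² = 62.8, so 63 per arm and 126 in total, for a standardised difference of 0.5. That is a separate matter, and nothing here depends on it. The article gives no adherence rate and does not say how much of the effect one session should produce, so no loss of effect or power at week 1 can be derived from it.

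**The case against.** The strongest defence is that measuring an early and then a sustained response is an ordinary design. By week 1 the randomised contrast is already active: social support was raised at the first session and the partner has been asked for a schedule. Timing is identical in both arms, so the week-1 comparison is not biased. All of this stands. It means that week 1 is worth measuring and reporting, but not that it should answer the primary objective.

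A second defence is that sizing the trial on 12 weeks already marks week 12 as the main time point. That supports the fix, but the Abstract, 2.3.2 and 2.9 do not say so. Nor is this a detail that a condensed article merely leaves out: the article itself lists and tests week 1 on equal terms.

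A third is that week 6 is not the end of delivery either, since the intervention therapist contacts the partner in weeks 6 and 10. Section 2.4 describes those contacts as checking whether support was given, not as sessions. Even so, they are a further reason to conclude at week 12 and not to pool weeks 6 and 12.

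A reader might go further and infer any of the following. The documents do not support them.

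- *The treating therapist runs the week-1 measurement, contrary to the Discussion's statement that* "measurements will not be performed by the treating physiotherapist". The week-1 wear instruction names no actor. Section 2.1 trains control therapists in "treatment of illness beliefs, the activity advice, and the use of the activity monitor", and intervention therapists in the same elements, but it also trains assessors in the monitor. Section 2.8 has the assessor collect Activ8 outcomes with no exception for week 1. At most, 2.4 does not say who issues the week-1 monitor. Naming the assessor would settle that but would not in itself secure blinding, since 2.4 has the randomisation centre tell the assessor the allocation.
- *The wear instruction favours one arm at week 1.* It is given in both groups, and both types of therapist are instructed on the monitor.
- *A trend in adherence over the three weeks is confounded.* No such trend is modelled. The time series analysis in 2.9 concerns illness beliefs.

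**Conclusion.** The point holds as a mismatch between what week 1 measures and the standing it is given. Week 1 follows one of two planned sessions, weeks 6 and 12 follow both, and all three are tested as the primary outcome although the trial is sized on 12 weeks. The week-1 comparison is valid and unbiased by timing, but it estimates the effect of early, partial delivery and should not by itself support a conclusion on the primary objective.

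The size is the session count only (50% against 100%). This rests on reading 2.4 as chronological, which its wording supports, and on counting the two sessions alike, which the article neither states nor rules out. The problem limits what may be concluded from week 1. It does not damage the week-12 comparison, and it is easily corrected.

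**What to change.** In 2.3.2 and 2.9, state that the primary objective is concluded on the between-group comparison of the proportion adherent at week 12, which is the time point of the sample size and comes after both sessions. Report week 1 as an early response after the first session and week 6 as supportive. Bring the Abstract into line. Optionally, add a few words to 2.4 on who issues the week-1 monitor.

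The cost is wording only: visits, measurements, sample size and treatment stay as they are. The small downside is that week 1 can no longer support a claim of effect on its own. A side benefit is that the primary conclusion then rests on one test instead of three.
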